### Eligibility criteria

Patients ≥18 yr of age with an established diagnosis of CNO are the population base of this study. In the absence of validated classification criteria for CNO, the primary diagnostic criterion is sterile bone inflammation at one or more skeletal sites in the anterior chest wall, with or without involvement of other skeletal sites. This is identified based on clinical features (inflammatory bone pain and possibly signs of inflammation on physical exam), biochemical markers (mild to moderate increase in inflammation markers, though often these are within normal range), and imaging findings (bone marrow edema, sclerosis, hyperostosis, erosions, ligament ossification, ankylosis of joints, and increased isotope uptake on nuclear imaging). If a bone biopsy is performed, histopathology compatible with sterile bone inflammation includes nonspecific inflammation and increased bone turnover. Sterile bone inflammation, and herewith diagnosis of CNO, is confirmed through a multidisciplinary, integrated assessment. Of note, this definition of sterile bone inflammation/CNO means that patients can have varying skeletal distribution patterns and may or may not have additional (extra)skeletal features such as arthritis, enthesitis, sacroiliitis, palmoplantar pustulosis, psoriasis, or severe acne.

Further inclusion criteria are as follows:

Score for maximal pain (concerning bone pain at lesion sites over the past week) ≥6/10 as measured by Brief Pain Inventory (BPI).^30^Insufficient response to at least one NSAID/COXIB at maximum approved and tolerated dosage, intolerance or contraindication to these agents, or indication for direct second-line treatment due to active vertebral lesions.A washout period of prior bisphosphonates (6 mo since last administration).

Exclusion criteria are as follows:

<18 yr of age.Active pregnancy wish, active pregnancy, or nursing.Generalized pain without pain at the site of CNO lesions.Bisphosphonate allergy.Estimated glomerular filtration rate < 30 ml/min.Uncontrolled endocrine comorbidities, active cancer (treatment), or other severe comorbidity preventing the attendance of study visits.Severe language barrier preventing the completion of questionnaires.Mental disability.

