### Outcomes and statistical analyses

The primary outcome of this trial is score of maximal pain on BPI (numerical rating scale 0-10) measured at the end of the 6-mo randomized phase. We will compare the difference between groups by generalized linear mixed model (GLMM) with analysis of covariance (ANCOVA) to account for baseline scores. The primary analysis will be intention-to-treat (see Table 1 and Figure 2). Secondary outcomes include a range of patient-reported,^32^^-^^40^ biochemical, and radiological outcomes, as well as their intercorrelation, baseline factors associated with treatment response,^41^^,^^42^ and cost-effectiveness^43^ (see Table 1 for measurement instruments, statistical analyses, and timepoints). Sensitivity analyses include a per-protocol and an as-treated analysis of the primary outcome. Missing data on the outcomes not evaluated by GLMM are imputed and handled through maximum likelihood techniques. No interim analyses are conducted.

**Table 1 TB1:** Primary and secondary outcomes of the PAM-CNO trial.

	**Outcome**	**Instrument**	**Timepoint of collection**	**Statistical analysis**	**Timepoint of analysis**
**Primary**	Score for maximal pain at CNO lesion sites	BPI	0, 3, 6, 9 and 12 mo	GLMM with ANCOVA	6 mo
**Secondary**	Score for minimal, average, and activity-related pain at CNO lesion sites	BPI	0, 3, 6, 9 and 12 mo	GLMM with ANCOVA	6 and 12 mo
**PROMs**	Shoulder function	SFA			
		SRQ			
	General health	SF-36			
	Quality of Life	EQ-5D			
	Work activity	Work Activity Score			
	Physical activity	IPAQ			
	Fatigue	MVI-20			
	Patient global	PGIC			
	Burden of a relative	Carer-QoL			
	Pain diary	NRS 0-10 for pain	2 d per wk, for entire 1-yr trial span	GLMM	6 and 12 mo
	Achievement of mild pain, as defined by ≤4/10 for maximal pain on BPI	BPI	0, 3, 6, 9, and 12 mo	Chi-square between groups, reported as odds ratio with 95% confidence interval	3, 6, and 12 mo
	Achievement of ≥50% reduction in maximal pain on BPI	BPI	0, 3, 6, 9, and 12 mo		
	% of patients with reduction in standard dose of NSAIDs/COXIBs	-	3, 6, and 12 mo		
**Biochemical**	ESR, CRP	Standard laboratory evaluation	0, 3, 6, 9, and 12 mo	GLMM with ANCOVA	6 and 12 mo
	Pro- and anti-inflammatory cytokines	ELISA			
	Bone markers	ELISA			
	mRNA expression	MLPA	0, 6, and 12 mo		
	T-lymphocyte counts	FACS			

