### Sample size

Based on our observational data on adult CNO patients with a maximum pain score of ≥6/10 treated with intravenous pamidronate, BPI score for maximal pain is expected to decrease from a mean of 8 with standard deviation (±) of 2 to a mean of 6 ± 2 in the active treatment arm. In rheumatoid arthritis, the placebo effect on pain has been estimated at 16-22 at a 100-mm scale.^44^ However, because evidence-based treatments for CNO are entirely lacking—potentially reducing patient confidence in any given treatment—and many patients present with advanced disease due to diagnostic delays, we anticipate a smaller effect in the placebo arm of this trial, with pain levels decreasing from 8 ± 2 to 7.5 ± 2. We use a power of 80% and an alpha of 0.05. As the primary analysis is done with ANCOVA, adjustment for correlation between baseline and follow-up scores was done (Pearson’s correlation coefficient calculated at 0.479), with a required sample size of 35 patients per arm (total *n* = 70).^45^ In case of screen failure or drop-out before the 6-mo primary endpoint, patients will be replaced to meet the required sample of 70.

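### For maximal BPI pain ≤4/10, Table 1 plans an unadjusted chi-square that ignores baseline pain: valid under randomisation, but adjustment would give modestly better precision

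*Protocol article*

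**What the plan says.** Table 1 (protocol article, Outcomes and statistical analyses) lists the outcome "Achievement of mild pain, as defined by ≤4/10 for maximal pain on BPI", analysed at 3, 6 and 12 months by "Chi-square between groups, reported as odds ratio with 95% confidence interval". No covariate is named. The method cell is blank for the next row, "Achievement of ≥50% reduction in maximal pain on BPI", so the same method evidently carries down.

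The primary outcome is the same BPI item kept as a score. It is analysed by "generalized linear mixed model (GLMM) with analysis of covariance (ANCOVA) to account for baseline scores".

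Eligibility criteria require "Score for maximal pain (concerning bone pain at lesion sites over the past week) ≥6/10". Sample size expects maximal pain to fall from 8 ± 2 "to a mean of 6 ± 2 in the active treatment arm" and to 7.5 ± 2 on placebo, with a baseline to follow-up correlation of 0.479 and 35 patients per arm. The Blinding section describes 1:1 allocation in blocks of 2, 4 and 6 and mentions no stratification by baseline pain.

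**The concern.** The cut-off is fixed, but the distance to it is not. A patient who enters at 6 reaches it with a 2-point fall, while one who enters at 10 needs 6 points. Baseline pain is therefore prognostic for this outcome, and the chi-square does not use it. With 35 per arm and no stratification, baseline pain is balanced only by chance, and any imbalance passes into the reported odds ratio. The primary model guards against this on the same item and the responder analysis does not. At stake are some precision and the robustness of one secondary result that clinicians are likely to read closely.

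**Working it through.** The article gives no power or event figure for the responder outcomes, so there is nothing of its own to reproduce. I take 35 per arm as given and work at 6 months.

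**Inputs.** From Sample size: follow-up mean 6 (pamidronate) and 7.5 (placebo), SD 2, baseline mean 8, SD 2, r = 0.479. From Eligibility criteria: baseline 6 to 10. Assumed: normal scores and a common slope. Within 6 to 10 and with mean 8, an SD of 2 is possible only if half the patients score 6 and half score 10, so I also show an assumed baseline SD of 1.26. The cut-off c is 4 on a continuous scale, or 4.5 if whole-number scoring is mimicked.

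**1. How strongly baseline grades the outcome.** At baseline b, P(≤4) = Φ{[c − m − s(b − 8)] / d}, where m is the arm's follow-up mean, s = 0.479 × 2 / (baseline SD) and d = 2√(1 − 0.479²) = 1.756.

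- Baseline SD 2, c = 4, pamidronate: at b = 6, (4 − 6 + 0.958)/1.756 = −0.59, giving 27.6%. At b = 8, 12.7%. At b = 10, (4 − 6 − 0.958)/1.756 = −1.68, giving 4.6%. Placebo: 7.4%, 2.3% and 0.6%.
- Baseline SD 1.26, c = 4.5, pamidronate: s = 0.760, and b = 6 to 10 gives 50%, 34%, 20%, 10% and 4%.

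The gradient is about six-fold under the first set and steeper under the second.

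**2. Chance imbalance.** The standard error of the baseline difference is 2√(2/35) = 0.478, which shifts the follow-up difference by 0.479 × 0.478 = 0.229. With baseline SD 1.26 it is 0.301 × 0.760 = 0.229, the same. With c = 4 the marginal rates are 15.9% and 4.0%, an odds ratio of 4.5. Splitting the shift equally between the arms gives 14.5% against 4.5% (odds ratio 3.6) or 17.3% against 3.5% (5.7).

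For scale, the expected counts are 5.6 of 35 and 1.4 of 35, so the standard error of the log odds ratio is about √(1/5.6 + 1/29.4 + 1/1.4 + 1/33.6) = 0.98. The shift is ln(5.7/4.5) = 0.24, about a quarter of that.

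**3. Number of responders.** 35 × (0.227 + 0.067) = 10.3 in total with c = 4.5, or 35 × (0.159 + 0.040) = 7.0 with c = 4. This decides which adjusted method is usable.

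**4. Which adjustment (simulated trials, 35 per arm, ≤4/10).**

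- Plain likelihood-ratio logistic test: type I error 8% to 9% at a nominal 5%.
- Wald test: power 14% against 41% for chi-square with baseline SD 2, and 37% against 49% with baseline limited to 6 to 10.
- Firth-penalised logistic, baseline over 6 to 10: type I error 2.7% to 5.6%; power 51% against 50% for chi-square at the planned effect, and 80% against 78% at a larger one.
- SD of the risk difference: 0.0765 standardised against 0.0814 unadjusted. (0.0765/0.0814)² = 0.88, so about 12% less variance, part of it Firth shrinkage.

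**5. The ≥50% reduction outcome.** Here the cut-off scales with baseline. With baseline SD 2, pamidronate response is 12.2%, 12.7% and 13.2% at baseline 6, 8 and 10. With the narrower spread it runs from about 20% to 8%, but adjustment still brings no gain: power is 46% adjusted against 52% for chi-square.

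**The case against.** The strongest objection is that nothing is wrong: under 1:1 randomisation the chi-square is a valid test of the marginal effect, the same BPI item already receives baseline adjustment in the primary analysis, and a simple comparison for a supportive dichotomy is common. Validity stands in full, and it limits the point to precision.

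It can also be said that adjustment may do harm. With so few events the ordinary likelihood-ratio test rejects too often and the Wald test loses power. The adjusted odds ratio is also a different quantity: about 6.2 at baseline 8, against 4.5 marginally. That stands too. It rules out ordinary logistic regression and requires a standardised risk difference beside the odds ratio.

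A reader might infer more than the document supports:

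- *That baseline largely decides who responds.* An r of 0.479 gives r² = 0.23, so most of the follow-up variance lies elsewhere.
- *That every chi-square outcome in the block needs replacing.* The ≥50% outcome gains nothing from adjustment.
- *That the share "of patients with reduction in standard dose of NSAIDs/COXIBs" is diluted by patients who cannot take these drugs.* Eligibility does admit patients with "intolerance or contraindication to these agents", but Table 1 does not say that the denominator is all patients. An article may leave that detail to the full protocol or SAP.

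**Conclusion.** The point holds as a minor improvement to one secondary outcome. Table 1 fixes a method for ≤4/10 that leaves out a prognostic baseline which the trial collects and already uses in its primary model. There is no bias and no invalid test. The expected gain is about 10% less variance of the risk difference and 0 to 3 points of power, plus protection against an imbalance that could move the odds ratio by roughly a quarter in either direction.

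These sizes rest on the article's planning means, follow-up SD and correlation, on normal scores with a common slope, and on an assumed baseline spread within 6 to 10. The direction does not depend on the spread, but the steepness of the gradient does. The figures are for 6 months only.

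**What to change.** For the ≤4/10 outcome only, replace the chi-square in the analysis wording with Firth-penalised logistic regression on arm and baseline maximal BPI, using a penalised profile-likelihood interval. Do not use plain likelihood-ratio or Wald inference, since only about 10 responders in total are expected. Report the standardised risk difference beside the odds ratio, and label the odds ratio as conditional on baseline. The unadjusted odds ratio may stay as supportive. Leave the chi-square for ≥50% reduction.

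The change needs no new data and should be recorded before unblinding. Its costs are one extra estimate to report, an odds ratio that no longer has a marginal meaning, and a test that is slightly conservative when events are few.

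### At the planned 6-month pain levels, the responder outcomes may have no finite odds ratio, so the odds ratio should not be the only effect measure reported

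*Protocol article*

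**What the plan says.** In the protocol article, Outcomes and statistical analyses, Table 1 lists two pain-responder outcomes among the secondary outcomes: "Achievement of mild pain, as defined by ≤4/10 for maximal pain on BPI" and "Achievement of ≥50% reduction in maximal pain on BPI". Both are analysed at 3, 6 and 12 months, and the analysis cell reads "Chi-square between groups, reported as odds ratio with 95% confidence interval". The article names no interval method, no continuity correction and no rule for an empty cell.

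The Sample size section gives no responder rates but fixes the quantities that imply them. In the active arm maximal pain "is expected to decrease from a mean of 8 with standard deviation (±) of 2 to a mean of 6 ± 2". A smaller effect is expected on placebo, "with pain levels decreasing from 8 ± 2 to 7.5 ± 2". The baseline to follow-up correlation is given ("Pearson’s correlation coefficient calculated at 0.479"), and 35 patients per arm are planned.

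**The concern.** If few placebo patients respond, an odds ratio is a fragile summary. With no placebo responder it has no finite sample value. With one or two, its interval becomes very wide and can include 1 beside a nominally significant chi-square test. A report with no finite estimate, or with a significant p-value next to an interval that includes no effect, would be hard to interpret. The planning assumptions put the placebo arm in this range at 6 months.

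**Working it through.** The plan states no responder rate or responder power, so there is no figure of its own to reproduce. The 35 per arm is taken as given.

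**Inputs (Sample size section).** 6-month mean μ = 6 (pamidronate) and 7.5 (placebo); baseline mean 8; SD 2 throughout; r = 0.479; n = 35 per arm. Assumption: scores are normal, taken either as continuous or as rounded to whole numbers.

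**Step 1: rate of ≤4/10.**
- Rounded, P = Φ((4.5 − μ)/2): placebo Φ(−1.5) = 6.7%, or 2.3 of 35; pamidronate Φ(−0.75) = 22.7%, or 7.9 of 35.
- Unrounded, P = Φ((4 − μ)/2): placebo Φ(−1.75) = 4.0%, or 1.4 of 35; pamidronate Φ(−1) = 15.9%, or 5.6 of 35.

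**Step 2: rate of ≥50% reduction.** Response means follow-up − ½ × baseline ≤ 0.
- This difference has mean μ − 4 and variance 4 + 1 − 2 × 0.5 × 0.479 × 4 = 3.084, so SD 1.756.
- Unrounded: placebo Φ(−3.5/1.756) = 2.3%, or 0.8 of 35; pamidronate Φ(−2/1.756) = 12.7%, or 4.5 of 35.
- Rounded: 3.2% (1.1) against 15.8% (5.5).
- Baselines confined to the entry range 6-10, with a smaller baseline SD of 1.41-1.60, give up to about 1.3 against 6.

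**Step 3: chance of no placebo responder, (1 − p)^35.**
- ≤4/10: 0.933^35 = 9% to 0.960^35 = 24%.
- ≥50% reduction: with 1.3 of 35 expected, 0.963^35 = 27%; with p = 2.3%, 0.977^35 = 44%.

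These figures do not depend on which interval is used.

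**Step 4: test against interval.** All 36 × 36 possible tables were enumerated. The test was uncorrected Pearson and the interval Woolf's, ln OR ± 1.96 √(1/a + 1/b + 1/c + 1/d), with 0.5 added to each cell when one is zero. Both choices are assumptions.

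| Outcome | Pearson p < 0.05, Woolf interval includes 1 | Yates and Woolf disagree, either direction |
|---|---|---|
| ≤4/10 | 13-25% of trials | about 4-5% |
| ≥50% reduction | 27-32% of trials | about 5-6% |

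Example close to the rounded expectation for ≤4/10, 8/35 against 2/35:
- χ² = 70 × (8 × 33 − 2 × 27)² / (35 × 35 × 10 × 60) = 4.2, p = 0.040.
- OR = 264/54 = 4.89; SE = √(1/8 + 1/27 + 1/2 + 1/33) = 0.832; interval 0.96 to 25.0.
- Yates p = 0.088, Fisher p = 0.084.
- Risk difference 17.1%, Miettinen-Nurminen interval 0.7% to 34.5%.

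Example with an empty cell, 6/35 against 0/35:
- Pearson p = 0.010; OR with 0.5 added = 6.5 × 35.5 / (29.5 × 0.5) = 15.6, interval 0.85 to 289.
- Risk difference 17.1%, Miettinen-Nurminen interval 6.3% to 32.8%.

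**Step 5: sensitivity to the placebo effect.** The Sample size section also reports, for rheumatoid arthritis, that "the placebo effect on pain has been estimated at 16-22 at a 100-mm scale". That is 1.6-2.2 points, so a placebo mean of 8 − 1.6 = 6.4 to 8 − 2.2 = 5.8. An infinite odds ratio then occurs in 0-4% of trials, and Pearson-Woolf conflict in at most about 7%. In between, simulated conflict rates are 5% (≤4/10) and 15-16% (≥50% reduction) at a placebo mean of 7.0, and 1% and 5-6% at 6.5.

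**Step 6: the alternative interval.** In every scenario run at the planning means, the Miettinen-Nurminen interval for the risk difference gave the same decision as the uncorrected Pearson test. Newcombe's interval disagreed with it in 3-14% of trials.

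**The case against.** A chi-square test and an odds ratio address the same null hypothesis, so naming both is no contradiction. A reader might infer from Table 1 that the planned interval will contradict the planned test. The article does not support that: it names neither an uncorrected test nor Woolf's interval, and such details are commonly left to an analysis plan that is not shown here. With Yates correction most of the conflict goes. The tables that conflict are often ones where Fisher's test is not significant either, as with 8 against 2. An expected count below 5 arises in about 41-85% of trials for ≤4/10 and more than 80% for ≥50% reduction, so the uncorrected chi-square could be blamed as readily as the odds ratio. All of this stands, and it makes the conflict conditional.

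It would also go too far to say that the odds ratio is often infinite for both outcomes. That fits ≥50% reduction better than ≤4/10, where the risk may be as low as 9%. The rates depend on a normal model for a bounded whole-number scale and on the assumed placebo effect.

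The infinite estimate itself is not answered by these points. It follows from the effect measure that the article does fix, whatever the test variant or interval. The larger placebo effect, which would nearly remove it, is one that the Sample size section explicitly does not expect in this trial.

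**Conclusion.** The point holds in a limited form. On the plan's own 6-month figures and a normal model, the only effect measure named for the pain-responder outcomes has no finite sample value in about 9-24% of trials (≤4/10) and 27-44% (≥50% reduction). Conflict between test and interval, at 13-25% and 27-32%, is conditional on an uncorrected chi-square with a Woolf interval.

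Only the 6-month comparison is shown to be affected. No 3-month means are given, and by 12 months both arms have had open-label pamidronate. These are secondary outcomes, and the primary analysis of maximal pain is untouched. The change is worth making because it is nearly free, not because the trial's main conclusion is at risk.

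**What to change.** For the chi-square responder rows of Table 1, report the risk difference with a Miettinen-Nurminen score 95% interval. It is defined when a cell is zero and is consistent with the uncorrected Pearson test. State that the test is uncorrected, because the match does not carry over to Yates or Fisher. The odds ratio may stay alongside if it is given a score or Firth-penalised interval. Newcombe's interval should not be described as agreeing closely with the test at these counts.

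The change takes one line in the analysis plan, to be settled before unblinding, and the downside is one more summary measure to report. Recruitment, conduct and the primary analysis do not change.

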## Objectives

The primary objective of the PAM-CNO trial is to investigate the efficacy of intravenous pamidronate in reducing pain in adult CNO patients. Secondary objectives are to evaluate the effect of pamidronate on (1) a variety of patient-reported outcome measures (PROMs), (2) biochemical and immunological indices relevant to CNO, and (3) radiological parameters of disease activity and severity. Additional objectives are to evaluate baseline predictors of treatment response, to elucidate mechanisms by which pamidronate may reduce pain in CNO, and cost-effectiveness.

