**Radiological**	Progression or regression of either sclerosis, hyperostosis, erosions, ankylosis, or soft tissue calcification	[^18^F]NaF-PET/CT	0, 6, and 12 mo	Chi-square between groups, reported as odds ratio with 95% confidence interval	6 and 12 mo
	Quantitative isotope uptake in CNO-lesions by SUV_max_			GLMM with ANCOVA	6 and 12 mo
**Correlations**	SUV_max_ with maximal and average pain	[^18^F]NaF-PET/CT and BPI	0, 6, and 12 mo	Pearson’s R or Spearman’s Rho as appropriate	0, 6, and 12 mo
	SUV_max_ with ESR and CRP	[^18^F]NaF-PET/CT and standard laboratory evaluation	0, 6, and 12 mo		
**Predictors of treatment response**	Diagnostic delay (yr)	-	0 mo	GLMM in pamidronate group, with maximal pain score on BPI as outcome	6 mo
	Baseline lesional isotope uptake (SUV_max_)	[^18^F]NaF-PET/CT	0 mo		
	Degree of central sensitization	CSI	0, 6, and 12 mo		
	Degree of neuropathic pain	PAIN-DETECT	0, 6, and 12 mo		
	Baseline presence of erosions, hyperostosis, and/or ankylosis	[^18^F]NaF-PET/CT	0 mo		
	Baseline presence of elevated ESR and/or CRP	-	0 mo		
**Cost-effectiveness**	Trial-based cost-utility from a societal perspective in accordance with the Dutch health-economics guidelines	IPCQ	0, 3, 6, 9, and 12 mo	Trial-based cost-utility analysis with costs-per-quality adjusted life yr, based on net-benefit analysis and friction-cost method.	6 and 12 mo (extrapolated to life-long discounted time horizon)

Abbreviations: ANCOVA; Analysis of Covariance, [18F]NaF-PET/CT; Sodium-fluoride positron emission tomography, BPI; Brief Pain Inventory, CarerQoL; Care-related Quality of Life Instrument, CNO; Chronic Nonbacterial Osteitis, COXIBs; Cyclooxygenase 2 Inhibitors, CSI; Central Sensitization Inventory, FACS; Fluorescence Activated Cell Sorting, ELISA; enzyme-linked immunosorbent assay, EQ-5D; EuroQol 5-Dimension, ESR; Erythrocyte Sedimentation Rate; GLMM; Generalized Linear Mixed Model, IPAQ; International Physical Activity Questionnaire, MLPA; Multiplex Ligation-dependent Probe Amplification, MVI-20; Multidimensional Fatigue Inventory-20, NRS; Numerical Rating Scale, NSAIDs; Non-Steroidal Anti-Inflammatory Drugs, PGIC; Patient Global Impression of Change, SF-36; Short Form Health Survey, SRQ; Shoulder Rating Questionnaire, SUV_max_; Standardized Maximum Uptake Value.

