A third challenge encountered in this trial was the choice for the primary outcome of patient-reported pain. Ideally, we would use a composite score that includes patient-reported outcomes such as pain and objective measures of inflammatory activity, reflecting both patient relevance and the biological mechanisms of treatment. However, for CNO, no objective markers of inflammatory activity are currently proven. Systemic inflammation markers are suboptimal indicators of disease activity due to their frequently normal levels at diagnosis,^2^ and the same holds for radiologic signs of disease activity such as increased isotope uptake, since it has been shown to persist despite evident clinical improvement, which may prompt overtreatment.^49^ Consequently, we use patient-reported pain at the site of CNO bone lesions as the primary outcome of this trial. While this is most relevant for patients, it may be modulated via different mechanisms which may complicate interpretation of the results. Therefore, patients are clearly instructed to differentiate and score the nociceptive inflammatory bone pain.^53^ Additionally, neuropathic and nociplastic pain are measured with standardized questionnaires to explore their association with treatment response. Recognizing that radiologic signs of disease activity in CNO need to be further investigated, this trial includes quantified uptake on [^18^F]NaF-PET/CT in the secondary analyses. This imaging modality is sensitive for bone pathology and yields quantitative parameters of bone turnover, which have shown to be elevated in CNO lesions and correlate with ESR.^46^ The longitudinal data on quantified [^18^F]NaF uptake from this trial will further elucidate the working mechanism of pamidronate, revealing whether pamidronate can quantitatively reduce bone turnover, and whether a decrease is associated with a reduction in pain.

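### Table 1 links bone uptake to pain only by correlations of levels at each visit and by baseline uptake, which cannot answer the Discussion's question whether a fall in uptake goes with a fall in pain

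*Protocol article*

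**What the plan says.** The Objectives section of the protocol article lists among its additional objectives "to elucidate mechanisms by which pamidronate may reduce pain in CNO". The Discussion ties this to imaging: "The longitudinal data on quantified [^18^F]NaF uptake from this trial will further elucidate the working mechanism of pamidronate", and then names the two things to be learned, "whether pamidronate can quantitatively reduce bone turnover, and whether a decrease is associated with a reduction in pain".

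The section on outcomes and statistical analyses refers to Table 1 for methods and timepoints. Three parts of the table involve SUVmax in a way that could bear on this:

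- **Correlations.** "SUV_max_ with maximal and average pain", by "Pearson’s R or Spearman’s Rho as appropriate", with collection and analysis both at 0, 6 and 12 months. No change score is named.
- **Predictors of treatment response.** Baseline SUVmax enters a "GLMM in pamidronate group, with maximal pain score on BPI as outcome", analysed at 6 months.
- **Radiological outcomes.** SUVmax is compared between arms by GLMM with ANCOVA at 6 and 12 months. Pain is not in that model.

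**The concern.** The question in the Discussion concerns two changes within the same patient. The planned correlations concern two levels at the same visit, and at month 0 no change exists yet. A correlation of levels reflects stable differences between patients (more active lesions, more pain) as well as any shared response. It can be clearly positive when changes are unrelated, and weak when changes are closely related.

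The article gives its own reason to keep the two apart: the Discussion notes that raised isotope uptake can remain after patients have clearly improved. If levels persist while pain falls, levels say little about response.

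What is at stake is how the mechanistic result is read. A visit-wise correlation could be taken as evidence that falling turnover goes with falling pain, or a real relation between the changes could go unseen.

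**Working it through.** The plan states no figure for this analysis, so there is none to reproduce. Two checks apply.

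**1. Do same-visit correlations determine the correlation of changes?**

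Inputs:
- Pain autocorrelation, month 0 to 6: aP = 0.479 (Sample size section).
- SUVmax autocorrelation: aS = 0.5, 0.7, 0.85 (assumed; not in the article).
- Same-visit correlation of SUVmax with pain: r = 0.2, 0.4, 0.6 (assumed), equal at both visits.
- Cross-visit correlation of SUVmax with pain: c, taken as equal in both directions and left free.
- Unit variances.

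The covariance of the two changes is 2(r - c), and their variances are 2(1 - aS) and 2(1 - aP). So

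corr(change in SUVmax, change in pain) = (r - c) / sqrt[(1 - aS)(1 - aP)].

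The planned correlations estimate r. They carry no information on c. If c = r, the change-change correlation is exactly 0, however large r is.

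The values of c giving a valid 4×4 correlation matrix satisfy |r - c| ≤ sqrt[(1 - aS)(1 - aP)] and |r + c| ≤ sqrt[(1 + aS)(1 + aP)]. For r = 0.4:

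| aS | limit on \|r - c\| | limit on \|r + c\| | largest r + c needed for the full range |
|---|---|---|---|
| 0.5 | sqrt(0.5 × 0.521) = 0.510 | sqrt(1.5 × 1.479) = 1.489 | 0.8 + 0.510 = 1.310 |
| 0.7 | sqrt(0.3 × 0.521) = 0.395 | sqrt(1.7 × 1.479) = 1.586 | 0.8 + 0.395 = 1.195 |
| 0.85 | sqrt(0.15 × 0.521) = 0.280 | sqrt(1.85 × 1.479) = 1.654 | 0.8 + 0.280 = 1.080 |

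The second limit never binds, so the change-change correlation can lie anywhere from about -1 to +1. For r = 0.2 the result is the same. At r = 0.6 a restriction of any size appears only with aS = 0.5: c can be at most 1.489 - 0.6 = 0.889, so the lower end is (0.6 - 0.889)/0.510 = -0.57 and the range is -0.57 to +1.00. At aS = 0.7 the lower end is about -0.97, and at 0.85 about -1.

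**2. What would arm add, if the 6-month correlation used both arms together?**

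With 1:1 allocation and no relation within arms, effects of dS and dP (in within-arm SDs) induce

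r = 0.25·dS·dP / sqrt[(1 + dS²/4)(1 + dP²/4)].

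The pain effect follows from the Sample size section: dP = (7.5 - 6)/2 = 0.75. The uptake effect is assumed.

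- dS = 0.8: 0.150 / sqrt(1.160 × 1.1406) = 0.150/1.150 = 0.13.
- dS = 1.2: 0.225 / sqrt(1.360 × 1.1406) = 0.225/1.2455 = 0.18.

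By Fisher z with n = 70 and two-sided 0.05, such correlations reach significance in about 19% and 32% of trials: atanh(0.130) × sqrt(67) = 1.07 and atanh(0.181) × sqrt(67) = 1.50, each compared with 1.96.

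**The case against.** The strongest reply is that the correlation row need not be meant for the mechanism question. The Discussion names two possible uses of uptake, as an indicator of disease activity and of treatment response. Visit-wise correlations with pain and with ESR/CRP are a normal first look at the former. Mechanism is only an additional objective, the change question is worded only in the Discussion, and a fuller protocol exists. This stands as a reason to keep the row and to keep the weight modest. It does not close the gap: the article promises the change result and lists the methods, and no listed row gives it.

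Several stronger readings are tempting, and the article does not support them:

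- **That the 6-month correlation is confounded by arm.** Table 1 does not say whether it is pooled, within arm or adjusted. The predictor rows are restricted to the pamidronate group and this row is not, which suggests all patients, but that is inference. The second check is conditional on it.
- **That a significant visit-wise correlation would be a false positive.** If a level correlation of 0.30 truly exists, 70 patients detect it about 72% of the time by Fisher z. That is power for a real association, misleading only if read as one between changes.
- **That the trial will declare SUVmax a marker of response on this basis.** The Discussion is conditional and speaks of what later studies may consider. The randomised comparison of SUVmax between arms also tests directly whether uptake responds to treatment.
- **That ESR and CRP need the same change analysis.** No section poses a change question for them.

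**Conclusion.** The point holds: the stated methods cannot answer the stated question of whether a decrease in uptake accompanies a reduction in pain. The indeterminacy is essentially complete at a same-visit correlation of 0.4, where any change-change correlation from about -1 to +1 remains possible. That rests on assumed SUVmax autocorrelations of 0.5 to 0.85, equal same-visit correlations at both visits and symmetric cross-visit correlations. These are bounds on what is possible, not a forecast.

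The arm-induced correlation of about 0.13 to 0.18 is a smaller, conditional addition. It depends on an unadjusted analysis of both arms and on uptake effects that the article does not give. If the correlations are run within arm it disappears, and the mismatch between levels and changes remains.

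This is worth correcting, but it concerns a secondary, mechanistic question. The primary analysis, sample size and data collection are untouched.

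**What to change.** For the mechanism question, pre-specify one regression of 6-month maximal pain on baseline maximal pain, 0-to-6-month change in SUVmax, and arm, using patients from both arms. Report the SUVmax coefficient with its confidence interval as an association. Change in uptake is not randomised, so it is not proof of mediation.

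Name this model as the single analysis of the question. It is not interchangeable with an arm-adjusted correlation of the two change scores: the regression estimates the slope on baseline pain (about 0.479 under the equal SDs and correlation in the Sample size section), whereas a change score fixes it at 1.

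Keep the visit-wise correlations in Table 1, labelled descriptive, with the 6-month one adjusted for or stratified by arm.

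The cost is one extra secondary analysis and a few lines of text, best settled before unblinding. BPI and SUVmax are already collected at 0 and 6 months. As a guide to precision, a simple correlation of about tanh[(1.96 + 0.842)/sqrt(67)] = 0.33 is detectable with 80% power in 70 patients, against tanh[(1.96 + 0.842)/sqrt(32)] = 0.46 in one arm of 35. That favours using both arms.
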